### Survey development

To determine the comfort level of ICU nurses with the ChloraLock^TM^ device and trial protocol, we will administer a paper-based survey to nurses who treat a study participant (see Additional file 5). We developed a nine-item survey to assess the ease of study-related tasks, time for device use, and effectiveness of educational activities and support materials. These domains were selected after consultation with the ICU educator and ICU nurse champions for the ChloraLock^TM^ study. The survey was pilot tested using a convenience sample of six ICU RNs, and further refinement of the survey involved clinical sensibility testing using a convenience sample of six ICU RNs. Feedback was provided on appropriateness, redundancy, and completion time of the tool.

### Participant timeline

Participants will be enrolled in the trial from the time of randomization until they leave the ICU. As shown in Fig. 2, data will be collected for the duration of participant ICU admission. For all participants, blood cultures will be drawn at baseline and every 48 h until all CVCs have been discontinued. For patients allocated to CHG locking device, device use will be discontinued when the patient leaves the ICU or all venous catheters have been discontinued.

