Hospital mortality at 28 days								X

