### Criteria for discontinuing allocated intervention

For a given trial participant, exit criteria from the study and assigned intervention will be as follow:
Consent for ongoing study participation is withdrawn by the study participant or their substitute decision maker (SDM).All venous catheters are discontinued.Participant experiences an adverse reaction to CHG locking solution.Death or discharge from ICU.

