### Statistical analysis

Simple descriptive statistics will be used for feasibility outcomes and baseline demographics (Table 3). Continuous data will be tested for normality using histograms, Normal Q-Q plots, skewness, kurtosis, and the Shapiro–Wilk test. Normally distributed data will be summarized using mean and standard deviation, non-normal data will be summarized using median and interquartile range, and categorical variables will be summarized using number and percent proportion. The two treatment arms will be compared by simple statistics as the study may not be powered for the secondary outcomes. However, we will test group differences with either the independent-samples t-test or the Mann–Whitney U test. Somers’ delta (*d*) will be used to identify and measure the strength and direction of association that exists between two ordinal variables, particularly for the number of positive cultures. If there is a large treatment effect between groups, this may aid the sponsor in proceeding with larger RCT as required for regulatory approval within other countries. All statistical tests will be conducted using SPSS version 24 (IBM Corp, Armonk, NY).

**Table 3 Tab3:** Summary of primary and secondary outcomes for the ChloraLock^TM^ pilot trial

Pilot trial outcomes	Analysis	Pass threshold
Primary outcomes		
1. Consent rate: patients and SDMs approached who consent to randomization	Proportion	≥ 80%
2. Recruitment rate: eligible patients who are randomized	Proportion	≥ 80%
3. Protocol adherence: times ChloraLock^TM^ is used in conjunction with usual locking procedures	Proportion	≥ 90%
4. Comfort: staff comfort level with the device and trial protocol	Descriptive	NA
Secondary outcomes		
1. Central line colonization: assessed for each arm as positive central line culture and negative peripheral poke	Proportion	NA
2. Bacteremia: assessed for each arm as positive stab cultures	Proportion	NA
3. Clinical end points: LOS in ICU, LOS in hospital, ICU mortality at 28 days, hospital mortality at 28 days	Median or mean proportions	NA

Given the small sample size and the focus on feasibility outcomes, there will be no subgroup analyses or interim analyses. We will adhere to the intention to treat principle.

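### The stated end of participation and data collection does not fit hospital length of stay and 28-day hospital mortality, and the sections that set it disagree with each other

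*Protocol article*

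**What the plan says.** Four places in the protocol article set the end of observation.

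- **Criteria for discontinuing allocated intervention.** A single list is introduced by the words "exit criteria from the study and assigned intervention will be as follow". Besides withdrawal of consent, it contains "All venous catheters are discontinued", "Participant experiences an adverse reaction to CHG locking solution" and "Death or discharge from ICU".
- **Participant timeline.** "Participants will be enrolled in the trial from the time of randomization until they leave the ICU", and "data will be collected for the duration of participant ICU admission". The same section says separately that device use stops at ICU exit or once no venous catheter remains.
- **Table 1 (Study design).** All four clinical end points, including "Hospital mortality at 28 days", are marked in the close-out column, which is defined by discontinuation of the intervention.
- **Outcomes and Table 3.** The clinical end points are ICU stay, hospital stay, ICU mortality at 28 days and hospital mortality at 28 days.

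Two further statements bear on the point. Statistical analysis says "We will adhere to the intention to treat principle". Data collection and management names the hospital's electronic health record as the source of trial data.

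**The concern.** Hospital stay and 28-day hospital mortality are in general settled only after a patient has left the ICU, but the plan ends participation and data collection at or before that moment. If staff follow the text, hospital stay is cut off and the hospital mortality end point records little that ICU mortality does not.

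The discontinuation list raises a second problem. By merging the end of treatment with the end of participation, it may take patients out of observation while they are still in the ICU. One of its triggers, a reaction to the chlorhexidine (CHG) locking solution, arises in practice only in the device arm. An analysis of everyone as randomised needs outcomes for those patients too.

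The pilot is meant to test a protocol for a larger trial, so a follow-up rule that does not fit its end points could be carried forward.

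**Working it through.** The plan gives no figure on this point, so there is none to reproduce. The check sets the rules against the end points and then illustrates size under stated assumptions.

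**Step 1: what is known when observation ends, reading each rule literally**

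| Course of the patient | Hospital stay | 28-day hospital mortality | ICU stay and 28-day ICU mortality |
|---|---|---|---|
| Dies in the ICU by day 28 while in the study | known | known | known |
| Still in the ICU at day 28 | known only if the patient later dies in the ICU | known | known by ICU exit |
| Leaves the ICU alive for a ward before day 28 | not captured | not captured | known |
| Catheters all out, or CHG reaction, while in the ICU: Participant timeline governs | as in the rows above | as in the rows above | known |
| Same event: discontinuation list governs | not captured | not captured, if before day 28 | cut short at study exit |

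The third row shows the conflict with the outcomes. The last two rows show the conflict between the two sections. Table 1 does not resolve either: its close-out point is the end of the intervention, which can come before ICU exit, so even ICU stay may be unknown then.

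**Step 2: deaths missed**

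Let g be the share of 28-day in-hospital deaths that occur after ICU discharge. The document does not give g. The captured share is 1 − g.

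- g = 10%: 1 − 0.10 = 90% captured
- g = 30%: 1 − 0.30 = 70% captured
- g = 50%: 1 − 0.50 = 50% captured

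If g were equal in both arms, the observed risk difference would shrink by the same factor.

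**Step 3: worst-case bounds**

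The Sample size section plans 50 per arm. Let f be the share of each arm that leaves the study alive before day 28 with later status unrecorded (assumed; not in the document). With observed death proportions p1 (device) and p0 (usual care), the lower bound is p1 − (p0 + f) and the upper bound is (p1 + f) − p0. The width is therefore 2f.

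- f = 50%: 50 × 0.5 = 25 per arm unrecorded, width 2 × 0.5 = 1.0
- f = 70%: 50 × 0.7 = 35 per arm unrecorded, width 2 × 0.7 = 1.4
- f = 90%: 50 × 0.9 = 45 per arm unrecorded, width 2 × 0.9 = 1.8

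A risk difference can range over at most 2. These bounds show how little the data alone would settle; they do not estimate bias.

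**Step 4: the exit that arises in one arm**

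Each exit for a CHG reaction is 1/50 = 2% of the device arm. At assumed reaction rates of 2%, 5% and 10%, the expected numbers are 50 × 0.02 = 1, 50 × 0.05 = 2.5 and 50 × 0.10 = 5, against none in usual care. Relative to the Participant timeline rule, the extra loss is only the time from the reaction to ICU discharge, because ICU discharge then ends observation in both arms.

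**The case against.** The strongest reply is that the plan clearly intends to collect these outcomes. Outcomes says the clinical end points will be documented for each arm, and both hospital end points can normally be read from the electronic record already named as the data source. The discontinuation section is headed as being about the intervention, so its reference to leaving the study may be loose drafting. The Participant timeline partly separates the end of device use from the end of enrolment. Figure 2 and the full protocol are not shown.

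Much of this stands, and it limits what may be concluded. A reader might infer:

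- **That the outcomes are unobservable.** The documents do not support this. The data appear retrievable; it is the stated collection window that excludes them.
- **That the intention-to-treat commitment is contradicted.** It is not. Nothing reassigns or excludes anyone, and patients can still be analysed as randomised. Missing outcomes after exit would undermine that analysis without negating it.
- **That there is a sizeable one-sided bias from CHG reactions.** No reaction rate is given, known CHG allergy is an exclusion, and the added loss is limited as shown in Step 4.
- **That removal of all venous catheters definitely ends participation.** The two sections differ on this, so it is unsettled.

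What the reply does not remove is the conflict itself. Naming a data source does not extend the collection window. Nor is this a detail lost in condensing a protocol into an article: the article states the exit rule, the window, the close-out point and the outcomes, and they do not fit together.

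**Conclusion.** The point holds as an inconsistency in the current text. Read literally, the plan does not capture hospital stay for patients discharged alive from the ICU, and it misses in-hospital deaths between ICU discharge and day 28. If the discontinuation list governs, ICU stay and 28-day ICU mortality are also cut short for patients who exit while still in the ICU, and one route to that exit arises in practice only in the device arm.

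The numerical size is unknown because the document gives no rates for ICU discharge, post-ICU death or CHG reaction. The illustrations rest on assumed ranges: f from 50% to 90%, g from 10% to 50%, and reactions from 2% to 10%. The inconsistency itself depends on none of them.

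This should be fixed but is not critical. Consent, recruitment, adherence and staff comfort are unaffected, the clinical end points have no pass threshold, and the plan itself says the study may not be powered for secondary outcomes.

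**What to change.** Reconcile the passages without changing any treatment rule:

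1. In Criteria for discontinuing allocated intervention, separate the events that end the assigned intervention from those that end follow-up. Which events stop the device is for the investigators and is not at issue here.
2. In Participant timeline, state that length of stay (to hospital discharge) and in-hospital vital status (to day 28) are taken from the electronic health record for every randomised participant, whatever ended device use, unless consent to data use is withdrawn.
3. In Table 1, move the length-of-stay and mortality rows to a hospital-discharge/day-28 column.

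The cost is a minor amendment and some record review, with no added patient contact. Recruitment was under way when the article was submitted and the consent material is not shown, so the sponsor should check that consent covers record data after ICU discharge and apply the rule to participants already enrolled where it does.

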**Fig. 2 Fig2:**
[figure not shown]
Flow of participants

### Sample size

The target sample size for the ChloraLock^TM^ pilot trial is 100 participants, with 50 participants randomized to each group. It is not possible to know the standardized effect size of our proposed intervention. Our best guess is to refer to other trials; however, trials that utilize our device do not exist. To err on the side of caution, we made the conservative assumption of having a very small effect size. A pilot study of such effect size is recommended to enroll 50–75 in each treatment arm as per the non-central t-distribution approach. Our target sample size is consistent with current guidelines on sample size calculation for pilot RCTs [36, 37] and the available funding from the sponsor.

### Screening and recruitment

Patients in three ICUs in one hospital will be screened for eligibility daily excluding weekends by the research staff and eligibility confirmed by the treating team. Once a patient is deemed to satisfy all inclusion and none of the exclusion criteria, the research staff will approach either the patient or the SDM on file to provide detailed information about the study and seek consent for participation (Additional file 6). It will be made clear that study participation is voluntary and refusal to participate will not impact the medical care provided. If the patient is unable to communicate and the SDM is not present in the ward, consent may be obtained from the SDM via telephone if witnessed by another staff member. Once written informed consent has been obtained, the research team will unseal an opaque envelope in sequence to randomize patients to receive usual care or CHG locking device. Screening and enrolment will conclude once our target sample size is reached. A de-identified record of all patients who were deemed eligible for enrolment but were not randomized will be kept on file. The following are potential and anticipated reasons: (1) The patient or SDM declined consent; (2) The patient is unable to give consent or the SDM is not available; and (3) The ICU physician declined consent.

### Allocation and blinding

Randomization will be done in block sizes of 2, 4, 6, and 8 in a fixed 1:1 ratio by means of a statistical computer software, R v3.4.2. Using the list generated by this software, 100 opaque security envelopes containing a note indicating either ‘ChloraLock’ or ‘Standard Care’ will be prepared and sequentially numbered. Envelopes will be sealed by a third party member. No members of the study staff will be privy to the allocation sequence generated. Upon obtaining informed consent, the research staff will open the security envelope that corresponds with the patients study ID to determine allocation. It will not be possible to blind the research staff, physicians, and bedside nursing staff of participant assignment since these individuals need to be aware of allocation to implement the intervention. The principal investigator will be blinded to the study outcomes throughout the duration of the trial.

### Data collection and management

Data collection will be performed by a research assistant trained in the use of Data Collection Forms. Participant demographic data and ChloraLock^TM^ pilot trial data will be extracted from their electronic health records, which will be accessed via the electronic patient database at Hamilton Health Sciences. Data will first be recorded in paper-based Case Report Forms (CRFs) that will be stored in a locked office at the Thrombosis and Atherosclerosis Research Institute (TaARI). Data will then be entered in electronic CRFs in REDCap, with pre-programmed range checks to help ensure data quality. Paper-based screening logs will be kept in a locked office and outcome data will be stored on the Team Sepsis database, both located at TaARI. Routine source data verification will occur for all data collected including eligibility, daily data, protocol violations, adverse events (AEs), and serious adverse events (SAEs). Participant data will be retained for 25 years stored off-site using Iron Mountain.

### Statistical analysis

Simple descriptive statistics will be used for feasibility outcomes and baseline demographics (Table 3). Continuous data will be tested for normality using histograms, Normal Q-Q plots, skewness, kurtosis, and the Shapiro–Wilk test. Normally distributed data will be summarized using mean and standard deviation, non-normal data will be summarized using median and interquartile range, and categorical variables will be summarized using number and percent proportion. The two treatment arms will be compared by simple statistics as the study may not be powered for the secondary outcomes. However, we will test group differences with either the independent-samples t-test or the Mann–Whitney U test. Somers’ delta (*d*) will be used to identify and measure the strength and direction of association that exists between two ordinal variables, particularly for the number of positive cultures. If there is a large treatment effect between groups, this may aid the sponsor in proceeding with larger RCT as required for regulatory approval within other countries. All statistical tests will be conducted using SPSS version 24 (IBM Corp, Armonk, NY).

**Table 3 Tab3:** Summary of primary and secondary outcomes for the ChloraLock^TM^ pilot trial

Pilot trial outcomes	Analysis	Pass threshold
Primary outcomes		
1. Consent rate: patients and SDMs approached who consent to randomization	Proportion	≥ 80%
2. Recruitment rate: eligible patients who are randomized	Proportion	≥ 80%
3. Protocol adherence: times ChloraLock^TM^ is used in conjunction with usual locking procedures	Proportion	≥ 90%
4. Comfort: staff comfort level with the device and trial protocol	Descriptive	NA
Secondary outcomes		
1. Central line colonization: assessed for each arm as positive central line culture and negative peripheral poke	Proportion	NA
2. Bacteremia: assessed for each arm as positive stab cultures	Proportion	NA
3. Clinical end points: LOS in ICU, LOS in hospital, ICU mortality at 28 days, hospital mortality at 28 days	Median or mean proportions	NA

Given the small sample size and the focus on feasibility outcomes, there will be no subgroup analyses or interim analyses. We will adhere to the intention to treat principle.

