ARROW SS-14703	ARROW multi-lumen central venous catheter	Triple lumen (per lumen)	10.0	0.5
ARROW SI-09880	ARROW percutaneous sheath introducer set	Cordis (side-arm lumen of introducer)	10.0	2.5
PICC lines	PICC lines	PICC line (per lumen)	20.0	0.5
ARROW CA-22122-F	ARROW temporary two-lumen hemodialysis catheter	Temporary hemodialysis catheter 12Fr (per lumen)	10.0	2.5^a^
MAHURKAR Elite 8888212216	Covidien MAHURKAR elite acute hemodialysis dual lumen catheter kit 13.5Fr	Acute dual lumen hemodialysis catheter 13.5Fr (per lumen)	10.0	2.5^a^

^a^4% sodium citrate solution

**Additional file 4** Instructional video on procedures for participants allocated to CHG locking device.

A single set of blood cultures will be drawn from the CVC of all study participants every 48 h beginning on the day of study enrolment until the patient has all CVCs removed, has a documented infection, or leaves the ICU. Blood cultures will be analyzed for infectious organisms in the core laboratory of the HGH.

The bedside nursing staff will perform the assigned interventions. Bedside nurses will document flushing and instillation of CHG on study-specific logs, which will be checked daily by the research staff. The only exception to the above procedures is flushing and locking of temporary and acute dialysis catheters will be carried out using 4% Sodium Citrate solution rather than 0.9% NS.

We will approach principal investigators (PIs) and research coordinators of all other studies conducted in the ICU to determine co-enrolment eligibility.

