## Outcomes

The primary outcomes of the ChloraLock^TM^ pilot trial relate to the feasibility of conducting a larger RCT.
*Consent rate* will be measured as the proportion of patients and SDMs approached who consent to participate in the trial; a successful consent rate will be defined as ≥ 80%. Consent rates will be reviewed on a monthly basis to improve enrolment practices.*Recruitment rate* will be measured as the proportion of patients eligible to participate who are randomized to the trial; successful accrual will be defined as ≥ 80%; we anticipate achieving enrolment of 100 patients within 50 weeks with an average of 2 patients enrolled per week. Screening logs will be reviewed on a weekly basis to determine eligibility rates.*Protocol adherence* will be measured as the proportion of instances when ChloraLock^TM^ is used during flushing and locking procedures; since this will be difficult to capture in a busy ICU setting, flushing and locking logs will be used as a surrogate to capture adherence. Successful protocol adherence will be ≥ 90% compliance with device use.*Level of comfort with the trial protocol* staff comfort with ChloraLock^TM^ and the trial protocol will be measured using repeated surveys throughout the duration of the trial. Vetted suggestions will be incorporated into the protocol.

The ChloraLock^TM^ pilot trial also includes secondary, clinical outcomes related to the antimicrobial efficacy of the device and prevention of central line infections.
*Central line colonization*: Rates of central line colonization in each study arm will be documented. We will define central line colonization as a positive central line culture with concurrent negative peripheral stab culture. We will not order peripheral stab cultures to avoid harm, but will collect data from those ordered by the treating team.*Bacteremia*: Rates of bacteremia in each study arm will be documented. We will define bacteremia as a positive peripheral stab culture and correlations will be done with central line cultures.*Clinical end points* will be documented for each study arm:
LOS in ICULOS in hospitalICU mortality at 28 daysHospital mortality at 28 days

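### Somers' d on the raw number of positive cultures has no denominator, so any difference in follow-up between the arms enters the comparison

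*Protocol article*

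**What the plan says.** Outcomes lists colonization and bacteremia as secondary outcomes ("Rates of central line colonization in each study arm will be documented"). Table 3 summarises both as proportions, LOS as median or mean, and 28-day mortality as a proportion.

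The Statistical analysis section adds two comparative methods:

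- "we will test group differences with either the independent-samples t-test" or the Mann–Whitney U test.
- Somers' d, to "measure the strength and direction of association that exists between two ordinal variables, particularly for the number of positive cultures".

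Neither carries an exposure term. The same section says that a large difference between arms may help the sponsor move to a larger trial.

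Sampling is described in three places:

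- Interventions: one culture set from the CVC every 48 h from the day of enrolment, "until the patient has all CVCs removed, has a documented infection, or leaves the ICU".
- Participant timeline: "blood cultures will be drawn at baseline and every 48 h until all CVCs have been discontinued". The same paragraph ends participation when the patient leaves the ICU.
- Criteria for discontinuing allocated intervention: study exit includes "Death or discharge from ICU" and an adverse reaction to the CHG locking solution.

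The Background expresses CLABSI incidence with a denominator, up to 6.9 per 1000 catheter days.

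**The concern.** With a culture every 48 h, the number of positives a patient can accumulate is limited by the number of cultures drawn, which is set by how long the line stays in and the patient stays in the ICU. Under Interventions it is also cut off at documented infection. A patient whose infection is documented at the first follow-up culture can add at most 1 positive after baseline; a colonised patient sampled for 10 days can add 5. The raw count therefore mixes risk per culture with number of cultures, and Somers' d ranks patients on that mixture.

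Follow-up is determined after randomization, in a trial where clinicians, nurses and research staff know the allocation. One exit criterion, a reaction to the locking solution, can arise only in the device arm. The overall research question also hopes for better patient and hospital outcomes, which could themselves change length of stay. Equal exposure is plausible but not guaranteed.

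LOS has a related problem: an early death is recorded as a short stay.

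At stake is how a pilot difference is read. A contrast that partly reflects length of stay is a poor input to a decision on a larger trial, and a count without a denominator cannot be set against the incidence that the protocol quotes.

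**Working it through.** The protocol gives no figure for the expected number of positive cultures, so there is none to reproduce. It also gives no catheter stay and no per-culture positivity; both are assumptions below. The 48 h schedule, the stop rules and 50 patients per arm come from the protocol.

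**1. Count against stay, no device effect.** Take exponential catheter stay with mean m days and cultures on days 0, 2, 4 and so on. Expected cultures = 1 + 1/(exp(2/m) − 1).

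- m = 6: 1 + 1/(exp(0.333) − 1) = 1 + 2.53 = 3.53
- m = 10: 1 + 1/(exp(0.2) − 1) = 1 + 4.52 = 5.52

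At 5% positivity in both arms: 0.05 × 3.53 = 0.18 and 0.05 × 5.52 = 0.28 positives per patient. The ratio is 5.52/3.53 = 1.56, about 1.6.

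**2. Effect on Somers' d.** For two arms, d = 2U/(n₁n₂) − 1, where U is the Mann–Whitney statistic, so the Mann–Whitney p-value tests it. Simulation: 50 per arm, 3000 trials per scenario, stay = 2 days plus an exponential time, equal per-culture risk in both arms. The stop rule is represented by stopping at the first positive culture. Negative d favours the device.

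| Positivity | Stop rule | Equal stays (8 v 8 days): d; p<0.05 | Device 5 v control 8 days: d; p<0.05 | Ratio per culture, 5 v 8 days |
|---|---|---|---|---|
| 5% | no | 0.002; 5.0% | −0.058; 11.3% | 1.005 |
| 5% | yes | −0.003; 4.5% | −0.054; 10.5% | 1.015 |
| 10% | no | 0.001; 4.9% | −0.098; 17.6% | 0.991 |
| 10% | yes | 0.000; 4.8% | −0.085; 14.4% | 1.002 |
| 20% | no | −0.002; 5.1% | −0.146; 27.6% | 0.995 |
| 20% | yes | −0.001; 5.6% | −0.103; 19.4% | 0.999 |

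With equal stays the test holds its level. With unequal stays it favours the shorter-stay arm, while positives per culture drawn stay within 0.99 to 1.02.

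**3. A reversal is possible.** With device risk 1.5 times higher per culture (15% v 10%) and stays of 4 v 10 days, d = −0.084: the worse arm looks better. At 5 v 8 days d is +0.017, so reversal needs a large imbalance.

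**4. Stop rule alone, equal stays, risk halved.** At 5% v 10%, d moves from −0.161 to −0.152 and power from 43% to 41%. At 10% v 20%, d moves from −0.255 to −0.224 and power from 70% to 65%. The cap attenuates modestly.

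**5. Event numbers.** At 6.9 per 1000 catheter days and an assumed 4 to 14 days per patient: 50 × 4 × 6.9/1000 = 1.4 to 50 × 14 × 6.9/1000 = 4.8 CLABSI per arm.

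**6. The two stop rules.** Both texts end sampling at line removal, and both end follow-up at ICU exit. Only Interventions adds documented infection. An infected patient with a line still in place contributes different counts under the two texts.

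**The case against.** The strongest reply is that randomization should balance exposure, and with balanced exposure there is no distortion (step 2). That stands. No passage points to an imbalance of 6 v 10 days; those stays are illustrative. The count is also not a listed outcome in Outcomes or Table 3, efficacy is secondary, and the protocol concedes that power may be inadequate. That stands too, and it limits the weight of the point.

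A reader might infer more than the documents support:

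- That infected or dead patients score better in general. An infected patient does not outrank one with no positives. The cap helps that patient only against a colonised patient still being sampled, or where infection elsewhere stops sampling before any positive culture. Mortality at 28 days has a fixed horizon and counts death as the bad outcome.
- That this is the main efficacy comparison. It supplements the Table 3 proportions.
- That speaking of rates in Outcomes and proportions in Table 3 is a contradiction. This article uses rate to mean proportion, as its consent and recruitment definitions show.
- That the absence of a named test for binary outcomes is an error. That detail may sit in an analysis plan that is not shown.

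LOS is reported beside mortality, so shortening by death is partly visible already.

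What the reply does not remove is that the protocol names both the statistic and the raw count, and that this choice is sound only if follow-up happens to be equal.

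**Conclusion.** The point holds as an improvement to a secondary pilot analysis, not as a demonstrated bias. Somers' d on the raw count is interpretable as a device effect only if the arms have similar follow-up. Under assumed mean stays of 6 v 10 days the count ratio is about 1.6 with no device effect. Under assumed stays of 5 v 8 days, p<0.05 occurs in about 11% to 28% of null trials, against about 5% with equal stays. These sizes rest on assumed stays, on assumed positivity of 5% to 20%, and on a constant risk per culture. The change is worth making because the protocol allows a large difference to aid the decision on a larger trial. The difference between the two culture stopping rules stands on its own and must be reconciled.

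**What to change.** In Statistical analysis, replace or accompany Somers' d on the raw count with two measures by arm:

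1. Positive CVC cultures per culture drawn, as a rate ratio with 95% CI (log of cultures drawn as offset). Repeat positives within a patient are not independent, so the variance should be clustered by patient.
2. First positive CVC culture per 1000 catheter-days, as a rate ratio with 95% CI (log catheter-days as offset). This uses the same unit as the incidence in the Background.

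Keep the Table 3 proportions, and give mean cultures drawn and catheter-days by arm beside them, because the proportion ever positive also rises with stay (26.7% v 35.5% at 5 v 8 days with equal 10% risk). Present LOS alongside deaths, for example by survival status. Reconcile the culture stopping rule in Interventions (which includes documented infection) with Participant timeline ("until all CVCs have been discontinued").

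Cost: mainly wording. The article does not say that catheter start and stop dates or the number of cultures drawn are recorded, so these must be captured on the CRF if they are not already. Few events will give wide intervals, which should be reported as they are.
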